#### **5.4.3. Criteria to stop the study (outside of statistical considerations)**

The study stops 3 months after the inclusion of the last patient. Nevertheless, the study could be stopped earlier if the early sitting is shown deleterious to the patient outcome.

## **6. DATA MANAGEMENT AND STATISTICS**

### **6.1. *COLLECTION, MANAGEMENT AND SAFETY OF THE DATA***

#### **6.1.1. Data collection**

An electronic case report form (eCRF) will be created by the data management section of the Research department of Nantes university hospital. The software « CAPTURE SYSTEM » developed by CLINSIGHT will be used. All the information required by the protocol must be reported in the eCRF, which will contain the patient's follow up visits. It will enclose all the data in order to confirm that the protocol has been respected, and will be used to detect any issue with the protocol compliance. In the patient electronic file will also be reported all the data required to perform the analyses described in section #7.

A paper version (CRF) of the patient electronic file will be available to facilitate data collection during the visits. This version must then be reported on line.

**Access to the eCRF and to the corresponding database will be secured.** In each center, one person will be responsible for reporting the information in the eCRF. **A coding rule to keep the patient anonymous will be defined before starting using the electronic file.**

The filing of the CRF will be performed by the physician, physiotherapist and/or nurses in charge (in particular for the first sitting supervision).

#### **6.1.2. Data coding**

The patient coding rule will be as such: patients will be attributed an ID determined by the participation rank in the study for each center. This ID will be automatically calculated during the randomization process described in section # 7.2.8.

By signing up this protocol, the responsible person and all the co-investigators commit to maintain confidential the patient identity. The first letter of the last name, first name, the date of birth together with the patient rank in the study will be the only information noted in the eCRF, and will enable any going back to the CRF if needed afterwards. All the nominative data will be deleted.

#### **6.1.3. Data management**

Data collection will rely on a clinical database and the creation of masks as in the eCRF and in accordance with the protocol and current legislation. The structure of the database and the eCRF, will be approved by the principal investigator.

## **6.2. STATISTICS**

400 patients are anticipated in the study.

Statistical analyses will be performed by [name] [name], biostatistician – Clinical research department-Nantes university hospital.

### **6.2.1. Description of statistical methods, including any intermediate analysis**

All the collected parameters will be described in the 2 groups. Quantitative variables will be described using means, standard deviation, median, minimum and maximum. Qualitative data will be described using number and percentages for each modality.

#### Primary outcome

Percentage of the patients with a Rankin score [0-2] at 3 months will be compared between the two groups by a Chi square test.

If the test is not significant, a switch to a non inferiority will be performed. Bilateral confidence interval (CI) of 95% will then be calculated, and the inferior border of the CI will be compared to the non inferiority threshold of -5 %

A multivariate logistic regression model will be used in a second step to adjust on age and former (before the qualifying event) Rankin score.

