### **6.2.2. Statistical justification for the number of patients required**

In a meta-analysis of two pilot studies comparing an « early » to a « usual » mobilization procedure, Craig and coll. (9) showed that the percentage of patients with a Rankin score [0-2] was 34.7 % at 3 months in the « usual » group (n=49) versus 57.4 % in the « early » group (n=54).

In our study, we hypothesized that the functional outcome at 3 months assessed by the Rankin score will be better in the « early » group than in the « progressive » group, with a percentage of Rankin [0-2] of 35% in the « progressive » group and 50% in the « early » group. With an alpha risk of 5% and a power of 80% (bilateral), 183 patients per group are required to show a difference. Total number will then be 366 patients.

Percentage of poor tolerance during the first sitting is estimated between 5 and 10% in the 2 groups. As this may affect the Rankin score at 3 months, the number of patient to include has been increase to 400.

If the superiority of the « early » group is not statistically demonstrated, a switch to non inferiority could be undertaken. For this analysis, the non inferiority threshold is set at -5 % (maximum acceptable clinical difference). With 400 patients, non inferiority will be demonstrated if the real difference between the two groups is between 9 and 15%.

Reference: Committee for Proprietary Medical Products (CPMP). Points to consider on switching between superiority and non inferiority. 2000. European Medical Agencies (AMEA). CPMP/EWP/492/99.

The study will be undertaken in 11 centers. Each one, has the potential to recruit patients, with at least 300 cerebral infarction cases a year.

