### **6.2.3. Significance**

Significance is set at 5%. If a witch to non inferiority is done, bilateral confidence interval of 95% will be built and the inferior border will be compared to the non inferiority threshold set at -5%.

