#### **6.2.8. Randomization**

The randomization list will be created by a statistician from the clinical research department of Nantes university hospital. Randomization will be performed using blocks and a ratio of 1:1.

A sealed envelop that contains the randomization # and the group affiliation will be created for each patient. These envelops will be numbered and stored in each participating center. Each time a patient is included, the investigator will take the next envelop, following the numerical order.

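### The -5 point comparison is valid on the crude difference, but it forgoes the precision of the planned adjustment for age and pre-stroke Rankin; a standardised risk difference would use it

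*Protocol*

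**What the plan says.** Protocol section 6.2.1 (Primary outcome), repeated in the Abstract under Statistical analyses, sets three steps in order. The first is a chi-square test on the percentage with Rankin 0-2 at 3 months. The second applies if that test is not significant: "Bilateral confidence interval (CI) of 95% will then be calculated, and the inferior border of the CI will be compared to the non inferiority threshold", which is -5%. The third is the model: "A multivariate logistic regression model will be used in a second step to adjust on age and former (before the qualifying event) Rankin score".

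Section 6.2.3 restates the second step: "bilateral confidence interval of 95% will be built and the inferior border will be compared to the non inferiority threshold set at -5" per cent. Section 6.2.2 gives the margin its meaning: "the non inferiority threshold is set at -5 % (maximum acceptable clinical difference"). I read this as an absolute difference in percentage points.

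Section 6.2.7 uses the intention-to-treat population for superiority, with per protocol as a sensitivity analysis, and gives the two equal weight for non-inferiority. Both covariates are available at no extra cost: date of birth and pre-stroke Rankin score are recorded at the inclusion visit (section 5.2).

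The protocol does not name the effect measure of the logistic model and gives the model no part in the non-inferiority decision.

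**The concern.** The fallback to non-inferiority is used only when superiority has failed, which is when the true difference is likely to be small and the interval width decides the result. An interval that ignores two baseline variables is wider than it need be if those variables predict the 3-month Rankin score. The trial plans to adjust for both, but only after the decision has been taken, in a model whose usual output is on a different scale from the margin. The adjusted result therefore cannot tighten the comparison with -5 points, and a reader who sees an adjusted odds ratio beside a crude difference is not told how the first bears on the margin.

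What is at stake is some power in both the superiority and the non-inferiority conclusions. Their validity is not in question.

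**Working it through.** **Inputs from the protocol.** Two-sided 5% and 80% power: "With an alpha risk of 5% and a power of 80% (bilateral), 183 patients per group are required to show a difference". Planning rates: "with a percentage of Rankin [0-2] of 35% in the « progressive » group and 50% in the « early » group". Allocation 1:1 (section 6.2.8). Total: "the number of patient to include has been increase to 400", so 200 per arm. Margin -5 points.

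**The plan's own sample size.** With mean proportion 0.425,

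n = [1.960·√(2·0.425·0.575) + 0.8416·√(0.35·0.65 + 0.50·0.50)]² / 0.15² = (1.370 + 0.582)² / 0.0225 ≈ 169.3, i.e. 170 per arm.

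The continuity correction gives (169.3/4)·[1 + √(1 + 4/(169.3·0.15))]² = 42.33·(2.076)² ≈ 182.4, i.e. 183. The stated figure is reproduced exactly, and it rests on an unadjusted comparison.

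**Non-inferiority power of the crude rule.** Power = Φ[(d + 0.05)/SE - 1.96], with SE = √{[0.35·0.65 + p(1 - p)]/200} and p = 0.35 + d.

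- d = 0: SE = 0.0477; 0.05/0.0477 - 1.96 = -0.91; power 18%.
- d = +5 points: SE = 0.0483; 0.10/0.0483 - 1.96 = 0.11; power 54%.
- d = +9 points: SE = 0.0487; 0.14/0.0487 - 1.96 = 0.92; power 82%.
- d = +15 points: SE = 0.0489; 0.20/0.0489 - 1.96 = 2.13; power 98%.

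This agrees with section 6.2.2, which expects non-inferiority to be shown for true differences of 9 to 15 points, if that is read as at least 80% power. At +9 the crude interval has a half-width of 1.96·0.0487 = 9.5 points.

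**Why the default model output does not fit the margin.** The odds ratio equal to a 5-point loss is [(c - 0.05)/(1.05 - c)] / [c/(1 - c)]. At c = 35% it is (0.30/0.70)/(0.35/0.65) = 0.80. At c = 50% it is (0.45/0.55)/1 = 0.82. Across the planning rates the equivalent hardly moves, but it is still a different quantity and no odds-ratio margin is stated. At rates outside the plan it drifts further: 0.78 at 75% and 0.75 at 80%. The conditional odds ratio is also non-collapsible, so it does not estimate the same effect as the crude difference.

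**What a smaller variance buys.** Multiplying SE² by a variance ratio v in the power formula gives:

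| True difference | v = 1 (crude) | v = 0.95 | v = 0.90 | v = 0.85 |
|---|---|---|---|---|
| 0 | 18% | 19% | 20% | 21% |
| +5 points | 54% | 56% | 59% | 61% |
| +9 points | 82% | 84% | 86% | 88% |

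A ratio of 0.90 is worth 400/0.90 - 400 ≈ 44 extra patients. It shortens the half-width at +9 from 9.5 to 9.5·√0.90 ≈ 9.0 points.

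**Which ratio to expect (assumption).** The protocol gives no prognostic strength for either covariate, so simulated trials of 400 patients with a 35% control rate were run over a range. The logistic model was standardised to a risk difference.

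- Log-odds of -0.6 per SD of age and -0.6 per pre-stroke Rankin grade: variance down about 10-15%; power from 54% to 59-60% at +5, and from 81-83% to 86-87% at +9.
- Half those strengths: variance down about 1-6%; power up 1-2 points.
- A separate simulation with one combined normal covariate, SD 0.3 to 1.3 on the logit scale: variance ratio 0.99 to 0.76 at +9. The upper end needs a very strong covariate and I do not rely on it.

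Under the stronger assumption, the rate of wrongly declaring non-inferiority at the margin stayed at about 2.5%. At a true difference of zero, the one-sided rate of declaring superiority was the same with and without adjustment (2.3% v 2.3% and 2.8% v 2.7% in two scenarios).

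**The case against.** The strongest reply is that nothing here is wrong. The crude interval and the margin are both differences in percentages, the model is explicitly a second step, and an unadjusted primary analysis with a supporting adjusted one is an accepted design. All of that stands.

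It can also be said that the effect measure of a supporting model belongs in the analysis plan foreseen in section 6.2.6. That holds for a supporting model. It holds less well for the choice of estimate that decides the trial, because sections 6.2.1 and 6.2.3 already fix that choice. In an open trial, a change to it is best written down before outcome data accumulate.

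The gain is assumed, and it may be negligible. Excluding patients with a prior Rankin above 3 narrows that covariate and limits what it can contribute. This also stands, and is why a range is given.

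Finally, the change costs some simplicity: a model-based estimate would replace the plain chi-square on which the 183 per group was calculated. That is a fair, small price to weigh.

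A reader might infer more than the text supports. One inference is that the adjustment cannot serve the non-inferiority decision at all. In fact the protocol names no effect measure, and predictions from the same model give a risk difference directly. Another is that the trial has two primary results on conflicting scales. In fact only the chi-square comparison is primary.

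**Conclusion.** The point holds as a minor efficiency improvement. The decision rule is valid and consistent with its margin, and the sample size reproduces. What the plan leaves unused is the precision from adjusting for two baseline variables that it already collects and already intends to model.

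With 200 per arm and a 35% control rate, non-inferiority power at a true +9 points would move from about 82% to 83-87%. The lower end corresponds to weak covariates (variance down about 1-6%) and the upper end to the stronger assumed effects (about 10-15%). The gain rests wholly on prognostic strengths that the documents do not give. Adjustment does not rescue the fallback when the arms are truly equal: power there stays near 20% under any of these ratios.

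**What to change.** In section 6.2.1, and correspondingly in 6.2.3 and the Abstract, state that the logistic model with treatment, age and pre-stroke Rankin will be used to predict each patient's probability of Rankin 0-2 under each arm. The difference of the averages, early minus progressive, is then reported with a two-sided 95% confidence interval.

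Name this standardised difference in advance as the governing estimate. Superiority is concluded if the interval lies above 0; otherwise its lower limit is compared with -5 points. The populations stay as section 6.2.7 sets them, with both intention-to-treat and per-protocol results required for non-inferiority. Make the switch depend on this interval instead of on the chi-square test, so that one interval serves both conclusions. Report the chi-square test, the crude difference and the odds ratio as supportive. Also state how the two covariates enter the model, how the variance is computed, and that the crude difference applies if the model cannot be fitted.

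The cost is a few sentences and a little programming. No new data are needed, and the 400 patients, the -5 point margin and the 5% level do not change. The one concession is that the primary estimate becomes model-based while the sample size remains justified by the unadjusted test. A line in section 6.2.2 can say so.

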#### Secondary outcome

- Clinical score (neurological deficit) based on the NIHSS at 7 days and 3 months: comparison of the mean scores between the two groups using a Student's test.
- Functional scale (Rankin score) at 7 days: comparison of the proportions of patients with a score [0-2] by a Chi square test.
- Autonomy scale (Barthel index) at 7 days and 3 months: comparison of the proportions of patients with a score < 60 (dependent) between the 2 groups using a Chi square or a Fisher test
- Length of stay: comparison of the means between the two groups using a Student's test
- Percentage of patient back home before 7 days or 3 months: Chi square test or Fisher test.
- Side effects associated with sitting in the two groups (tolerance of upright positioning in the early versus progressive arms) : description of the side effect in the 2 groups and comparison of the most frequent (>5%) by a Chi square test or a Fisher test.

- Prevalence of swallowing disturbance, pneumopathy, acute urinary retention, bladder catheterization, deep vein thrombosis during hospitalization: comparison between the two groups using a Chi square test or a Fisher test.
- Prevalence of post stroke fatigue: comparison between the two groups using a Chi square test or a Fisher test.

A multivariate logistic regression model will be used in a second step to adjust on age and former (before the qualifying event) Rankin score.

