| Statistical analyses | 
Primary outcome:
 
Percentage of the patients with a Rankin score [0-2] at 3 months will be compared between the two groups by a Chi square test.
 
If the test is not significant, a switch to a non inferiority will be performed. Bilateral confidence interval (CI) of 95% will then be calculated, and the inferior border of the CI will be compared to the non inferiority threshold of -5 %
 
A multivariate logistic regression model will be used in a second step to adjust on age and former (before the qualifying event) Rankin score.
 
Secondary outcomes:
 
 
- Clinical score (neurological deficit) based on the NIHSS at 7 days and 3 months: comparison of the mean scores between the two groups using a Student's test.
 
- Functional scale (Rankin score) at 7 days: comparison of the proportions of patients with a score [0-2] by a Chi square test.
 
- Autonomy scale (Barthel index) at 7 days and 3 months: comparison of the proportions of patients with a score < 60 (dependent) between the 2 groups using a Chi square or a Fisher test
 
- Length of stay: comparison of the means between the two groups using a Student's test
 
- Percentage of patients back at home before 7 days or 3 months: Chi square test or Fisher test.
 
- Side effects associated with sitting in the two groups (tolerance of upright positioning in the early versus progressive arms): description of the side effect in the 2 groups and comparison of the most frequent (>5%) by a Chi square test or a Fisher test.
 
- Prevalence of swallowing disturbance, pneumopathy, acute urinary retention, bladder catheterization, deep vein thrombosis during hospitalization: comparison between the two groups using a Chi square test or a Fisher test.
 
- Prevalence of post stroke fatigue: comparison between the two groups using a Chi square test or a Fisher test.
 
 
A multivariate logistic regression model will be used in a second step to adjust on age and former (before the qualifying event) Rankin score.
 |

|  |  |
|--|--|
|  |  |
|--|--|

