### **2.2. SECONDARY AIMS AND EVALUATION CRITERIA**

#### **2.2.1. Secondary aims**

To show that neurological deficits observed at 7 days and 3 months after stroke onset are improved in the « early sitting » group.

To show that the functional prognosis at 7 days after stroke onset is improved in the « early sitting » group.

To show that autonomy is improved at 7 days and 3 months in the « early sitting » group

To show that early sitting facilitates the process of going back home

To show that the length of stay is shorter in the « early sitting » group

To show that early sitting decreases the rate of complications related to immobilization.

To explore the tolerance of upright positioning in the two groups

To explore the prevalence of fatigue at 3 months after stroke in both groups.

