##### Autonomy scale: The Barthel index (annex #3)

The good reproducibility of this index makes it a good tool for clinical trials.

This index assessed the autonomy of the patient, from 10 everyday-life tasks, dealing with self-care and mobility. The score varies from 100 (completely independent) to 0 (completely dependent), a score below 60 is associated with dependence in general.

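### The Barthel index is tested only as below 60 versus 60 or more, so gains in autonomy that do not cross 60 cannot register; a full-index test is a cheap improvement

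*Protocol*

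**What the plan says.** The secondary aim in section 2.2.1 of the protocol is stated in terms of improvement: "To show that autonomy is improved at 7 days and 3 months" in the early group. Section 5.1.1 describes the instrument and gives the reason for the cut: "The score varies from 100 (completely independent) to 0 (completely dependent), a score below 60 is associated with dependence in general". Appendix 3 scores every item in steps of 5, so the total can take 100/5 + 1 = 21 values. Section 5.3 and the study schedule in section 5.2 have the index recorded at inclusion, at day 7 (or discharge if earlier) and at 3 months.

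The planned test appears in section 6.2.1 (Secondary outcome): "Autonomy scale (Barthel index) at 7 days and 3 months: comparison of the proportions of patients with a score < 60 (dependent"). The abstract has it in the same terms: "comparison of the proportions of patients with a score < 60 (dependent) between the 2 groups using a Chi square or a Fisher test". A logistic regression adjusting for age and pre-stroke Rankin follows as a second step. The only other use of the Barthel score is the general descriptive summary of quantitative variables at the start of section 6.2.1. Section 6.2.5 rules out imputation for secondary outcomes.

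**The concern.** The aim concerns the degree of autonomy, but the test sees two classes. Patients at 60 and at 100 count as equal, and so do patients at 0 and at 55. A patient who moves from 65 to 95, or from 10 to 50, contributes nothing to the comparison. The second-step logistic regression does not recover this if, as the text suggests, it models the same binary outcome.

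What is at stake is how a non-significant autonomy result would be read. If early sitting shifts patients along the whole scale, the cut test has less chance of showing it than a test using all the recorded levels, and a null result could be taken as no effect on autonomy. The full score is already collected, so the information is given up at the analysis stage only.

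**Working it through.** **Inputs from the protocol.** Section 6.2.2: "with a percentage of Rankin [0-2] of 35% in the « progressive » group and 50% in the « early » group", and "With an alpha risk of 5% and a power of 80% (bilateral), 183 patients per group are required to show a difference". The total is then raised: "the number of patient to include has been increase to 400". Section 6.2.8: "Randomization will be performed using blocks and a ratio of 1:1". This gives 200 per arm and a two-sided 5% level.

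**Step 1: the plan's own figure.** The protocol states no power for the Barthel index, so the only figure to reproduce is the 183 per group for the primary outcome. With mean proportion 0.425 and difference 0.15:

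- Uncorrected: n = [1.96·√(2·0.425·0.575) + 0.842·√(0.35·0.65 + 0.50·0.50)]² / 0.15² = 169.3, so 170.
- With continuity correction: n′ = (169.3/4)·[1 + √(1 + 4/(169.3·0.15))]² = 182.4, so 183.

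The stated figure is reproduced exactly.

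**Step 2: effect size.** The sizing rates imply an odds ratio of (0.50/0.50)/(0.35/0.65) = 1.857. Applying it to the Barthel index is an assumption.

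**Step 3: assumed Barthel distribution.** In the control arm, a share p lies below 60, spread evenly over the 12 levels 0-55. A share of 25% or 40% sits at 100. The rest is spread evenly over the 8 levels 60-95. The early arm follows from proportional odds at 1.857, so its share below 60 is q = o/(1 + o), with o = [p/(1 − p)]/1.857.

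**Step 4: power of the planned test.** Worked case p = 0.40: o = 0.6667/1.857 = 0.359, so q = 0.264. With mean share 0.332, the normal approximation gives

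Φ{[0.136·√200 − 1.96·√(2·0.332·0.668)] / √(0.40·0.60 + 0.264·0.736)} ≈ 0.825.

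The exact figure is 0.826. The table uses exact chi-square power. The Wilcoxon figures are tie-corrected, from 20,000 simulated trials per case, and span the two ceiling shares.

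| Controls below 60 | Early arm below 60 | Chi-square on the cut | Wilcoxon on full index |
|---|---|---|---|
| 15% | 8.7% | 50% | 92-94% |
| 20% | 11.9% | 61% | 92-94% |
| 30% | 18.8% | 75% | 92-94% |
| 40% | 26.4% | 83% | 92-94% |
| 50% | 35.0% | 86% | 92-94% |

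The loss runs from about 92 − 86 = 6 points to about 94 − 50 = 44 points. With an odds ratio of 1.5 and 30% at the ceiling, the figures are 27-52% against about 63%.

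**Step 5: sensitivity to the assumptions.**

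- An analytic calculation (Whitehead variance, ceiling shares from 25% to 55%) at odds ratio 1.857 gives losses of 8 points with 50% of controls below 60, 29 points with 20% and 51 points with 10%.
- With 60% or 65% below 60 and few at the ceiling, the same method gives 87% against 94.5% and 86% against 94.6%, a loss of about 8 points.
- With an odds ratio of 2.2 and 35-50% below 60, the loss shrinks to about 2 to 6 points. With only 5% below 60 at 1.857, it exceeds 60 points.
- If the effect lies wholly above 60, simulated chi-square power is about 5%, against 53% for the rank test.
- If the effect acts only across 60 (35% falling to 23%), chi-square has 76% against 25% for the rank test: the cut wins.

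**The case against.** The strongest defence is that the plan made a legitimate choice. The cut is pre-specified, identical in the abstract and section 6.2.1, and given a clinical reason in section 5.1.1. It fits the trial's own way of thinking: the primary outcome is also a dichotomy meant to capture autonomous living. The outcome is secondary and the trial is not sized on it. The full score will be described by arm, so a shift along the scale would be visible though untested. Section 6.2.5 supplies no value for patients who die, so a full-index test needs a rule that the protocol lacks. All of this stands. It limits the weight of the point and shapes the fix, but it does not supply a test of the full score.

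Three stronger readings are tempting, and the documents do not support them.

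- A reader might infer that few patients will score below 60 at 3 months, because NIHSS of 22 or more and pre-stroke Rankin above 3 are excluded, and so expect the larger losses. Section 6.2.2, however, plans for only 35% of the progressive arm at Rankin 0-2, hence 65% at 3 or worse, deaths included. The protocol gives no mapping from Rankin to Barthel, but this figure does not favour 15% below 60 over 40-50%.
- A reader might say that Barthel is singled out, since NIHSS is compared on its full range in the same list. The 7-day Rankin in that list is also graded and also dichotomised.
- A reader might take the loss as certain. It depends on an effect spread across the scale, and it reverses if the effect sits at the boundary.

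**Conclusion.** The point holds as a cheap improvement in efficiency. It is not an error or a contradiction in the plan. As written, the autonomy comparison at both visits cannot respond to changes that stay on one side of 60, although the stated aim is improvement in general and the full score is recorded.

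The size is illustrative. With 200 per arm with data, a proportional-odds effect of 1.857 and 15-50% of controls below 60, the planned test has about 50-86% power against about 92-94% for a rank test. At 40-50% below 60 the planned test still has 83-86%, above the 80% sought for the primary outcome, so it would be wrong to conclude that the autonomy comparison is generally underpowered. The range of 6 to 44 points is not a bound in either direction: other assumed shapes and effects give smaller or larger losses, and an effect confined to the boundary favours the cut. The protocol argues for no such boundary-only effect, which is why the full-index test is the better main comparison and the cut is worth keeping beside it.

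**What to change.** In section 6.2.1 and the abstract, at 7 days and at 3 months:

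- Make the main Barthel comparison a full-index analysis: a Wilcoxon rank-sum test, or a proportional-odds model adjusted for age, pre-stroke Rankin and inclusion Barthel. Name one of the two in advance.
- State that patients who have died by the visit receive the worst rank, below a Barthel score of 0. Note this as an explicit exception to the no-imputation rule in section 6.2.5.
- Keep the pre-specified proportion below 60, with its chi-square or Fisher test and a 95% CI for the difference, as the supportive clinical analysis. This preserves the readable result and covers the case of an effect at the boundary.

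A t test on the mean is less suitable because of the likely ceiling: with 55% of controls at 100 and an odds ratio of 1.65, simulated power was 62% against 73% for the rank test.

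The cost is wording and one more analysis per visit. No new data, visits or patients are needed. The drawback is that a rank or odds-ratio result is less direct to read than a percentage. The change can be recorded in the analysis plan that section 6.2.6 requires before the database is frozen.
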